# COMPASS: deCOMPressing stomA and two-Stage elective resection vs. emergency reSection in patients with left-sided obstructive colon cancer

**DOI:** 10.1186/s13063-023-07636-y

**Published:** 2023-10-05

**Keywords:** Colon cancer, Colorectal cancer, Obstruction, Emergency, Randomized controlled trial

## Abstract

**Background:**

Colorectal cancer stands as a prevalent cause of cancer-related mortality, necessitating effective treatment strategies. Acute colonic obstruction occurs in approximately 20% of patients and represents a surgical emergency with substantial morbidity and mortality. The optimal approach for managing left-sided colon cancer with acute colonic obstruction remains debatable, with no consensus on whether emergency resection or bridge-to-surgery, involving initial decompressing stoma and subsequent elective resection after recovery, should be employed. Current studies show a decrease in morbidity and short-term mortality for the bridge-to-surgery approach, yet it remains unclear if the long-term oncological outcome is equivalent to emergency resection.

**Methods:**

This prospective, randomized, multicenter trial aims to investigate the management of obstructive left-sided colon cancer in a comprehensive manner. The study will be conducted across 26 university hospitals and 40 academic hospitals in Germany. A total of 468 patients will be enrolled, providing a cohort of 420 evaluable patients, with an equal distribution of 210 patients in each treatment arm. Patients with left-sided colon cancer, defined as cancer between the left splenic flexure and > 12 cm ab ano and obstruction confirmed by X-ray or CT scan, are eligible. Randomization will be performed in a 1:1 ratio, assigning patients either to the oncological emergency resection group or the bridge-to-surgery group, wherein patients will undergo diverting stoma and subsequent elective oncological resection after recovery. The primary endpoint of this trial will be 120-day mortality, allowing for consideration of the time interval between diverting stoma and resection.

**Discussion:**

The findings derived from this trial possess the potential to reshape the current clinical approach of emergency resection for obstructive left-sided colon cancer by favoring the bridge-to-surgery practice, provided that a reduction in morbidity can be achieved without compromising the oncological long-term outcome.

**Trial registration:**

German Clinical Trials Register (DRKS) under the identifier DRKS00031827. Registered on May 15, 2023.

Protocol: 28.04.2023, protocol version 2.0F.

**Supplementary Information:**

The online version contains supplementary material available at 10.1186/s13063-023-07636-y.

## Introduction

Colorectal cancer is the third leading cause of cancer death in both men and women in the USA [1] and the second leading cause of cancer death in men and the third leading cause of cancer death in women in Europe [2]. Worldwide, colorectal cancer accounts for 19.0 million (18.5–19.5) disability-adjusted life years (DALYs) [3]. The risk of developing colorectal cancer increases with age. More than half of patients develop the disease after the age of 70; only about 10% of cancers occur before the age of 55. Approximately 20% of patients initially present with acute colonic obstruction, which represents one of the most common causes of surgical emergency [4, 5]. While the consensus for right-sided obstructive colon cancer is primary resection and ileocolic anastomosis [6], international guidelines do not agree on the optimal management of the much more common left-sided obstructive colon cancer [4]. The most recommended procedure for patients with left-sided obstructive colon cancer is the emergency resection (ER) with or without anastomosis, which is a risk factor for high morbidity and mortality [5, 7].

A study evaluating the Dutch surgical colorectal audit data between 2009 and 2013 found an overall mortality of 8.5% after emergency resection compared to 3.4% in elective surgery [5]. Furthermore, primary anastomosis was only achieved in 64% of emergency resections, with 5% end ileostomy and 21% end colostomy compared to over 90% primary anastomosis in elective surgery [8].

A major burden for patients after emergency colon cancer resection is the development of postoperative complications, prolonged intensive care unit stay, permanent stoma, and in-hospital death. Patients undergoing emergency resection for obstructive cancer have a significant risk of permanent stoma [8, 9] and up to 70% of stoma patients experience long-term dysfunction or complications that significantly reduce their quality of life [3, 10]. Finally, the socioeconomic burden of colon cancer must be considered, as the cost of care has increased significantly in recent years. Currently, 31% of costs are spent on complications, with a 196% increase in costs for patients with major complications [11]. Reducing mortality and morbidity after emergency resection for obstructive left-sided colon cancer could significantly reduce costs to the healthcare costs [12, 13].

Several studies have suggested two-staged approaches with primary bowel decompression, either through the use of self-expanding metallic stents (SEMS) or placement of a decompressing stoma (DS) as a bridge-to-surgery (BTS). This approach aims to relieve colonic obstruction and allows patients to undergo elective oncological hemicolectomy after recovery. The BTS approach is considered a feasible and safe alternative to emergency resection with the goal of reducing postoperative complications [7]. Previous studies have mainly focused on comparing SEMS versus emergency resection in obstructive left colon cancer. A recent representative meta-analysis by Jain et al. concludes that SEMS offers several advantages over emergency resection, including significantly lower rates of permanent stomas, decreased anastomotic leakage, and improved overall in-hospital mortality [7]. However, the placement of SEMS requires a high level of endoscopic expertise that may not be available in all hospitals. Moreover, there is still a lack of evidence regarding the oncological risks associated with microperforations during stenting. Several studies have suggested a potential increase in locoregional recurrence rates [14]. Conversely, the BTS approach, involving the placement of a decompressing stoma, presents a technically straightforward procedure that can be performed minimally invasively and universally in emergency scenarios [15].

To date, only one randomized study has compared the use of a decompressing stoma as a bridge to surgery with emergency resection. Despite the study’s limitations, including a small patient cohort (*n* = 121), an extended inclusion period (1978–1993), and the absence of minimally invasive techniques, Kronborg et al. observed a significant decrease in the incidence of permanent colostomies and a non-significant trend towards lower morbidity among patients undergoing a two-staged approach with a decompressing stoma [16].

A meta-analysis from 2015 summarizes the findings of eight comparative studies involving 2424 patients from 1977 to 2015 [17]. While the meta-analysis did not identify significant differences in 30-day mortality and morbidity between the treatment groups, patients who received a decompressing stoma before elective resection were more likely to undergo primary anastomoses and less likely to be left with a permanent stoma [17].

A recent retrospective propensity-score matched study by Veld, Tanis et al. demonstrated that the use of a decompressing stoma as part of the BTS approach resulted in a significantly decreased 90-day mortality rate compared to emergency resection (1.7% vs. 7.2%, *p* = 0.006) [18]. This difference was particularly pronounced in the patients over 70 years of age (3.5% vs. 13.7%, *p* = 0.027). Additionally, patients treated with a decompressing stoma underwent a higher proportion of minimally invasive resections (56.8% vs. 9.2%, *p* < 0.001) and had a greater incidence of primary anastomoses (88.5% vs. 40.7%, *p* < 0.001), a reduced occurrence of permanent stomas (23.4% vs. 42.4%, *p* < 0.001), and improved 3-year overall survival rates (79.4% vs. 73.3%, hazard ratio 0.36) [18].

These findings collectively suggest that the BTS approach for obstructive left-sided colon cancer has the potential to decrease perioperative mortality and improve quality of life by reducing the need for permanent stomas without compromising long-term oncological outcomes. However, it should be noted that the retrospective nature of the studies mentioned above precludes a comprehensive evaluation of dropout rates between decompressing stoma placement and subsequent resection. Thus, a prospective randomized trial is necessary to conduct an intention-to-treat analysis and validate these findings.

In this randomized multicenter trial, we aim to compare the outcomes of patients with obstructive left-sided colon cancer who undergo either emergency resection or the placement of a decompressing stoma as a bridge-to-surgery strategy.

## Methods

### Ethical approval and study registration

The COMPASS trial has obtained ethical approval from the ethical committee of the TU Dresden (Ethical Committee number EK-278062022). Furthermore, the trial has been registered on the 15 May 2023 in the German Clinical Trials Register (DRKS) under the identifier DRKS00031827 (https://drks.de/search/en/trial/DRKS00031827).

### Study design

The COMPASS trial is a multicenter, randomized, open-label study that will be conducted across 26 university hospitals and 40 academic hospitals in Germany. The trial was designed to show the superiority in regard to 120-day postoperative mortality among patients subjected to a two-stage bridge-to-surgery (BTS) procedure, as opposed to those undergoing a single-stage emergency resection (ER) for the management of obstructive left-sided colon cancer. Inclusion criteria involve patients presenting with symptoms of obstruction (abdominal distension, nausea, and/or vomiting) and having a left-sided colon tumor suspected of being colon cancer. Radiological assessments, including X-ray or a CT scan, must demonstrate a dilated colon with or without dilatation of the small intestine. Additionally, a high-grade suspicion of colon cancer should be identified on CT or endoscopy during the preoperative examination. Please refer to Fig. 1 for an illustration of the trial scheme.

**Fig. 1 Fig1:**
[figure not shown]
Flowchart of the trial scheme

### Stratification and randomization

Patient randomization will be performed using a secure online computer randomization system, either directly in the operating room or by the trial coordinator via phone. Block randomization will be employed to ensure balanced participant numbers throughout the trial. Stratification will be applied based on the following factors: age (younger or older than 70 years), tumor stage, gender, ASA classification (1–2 vs. 3), presence of small bowel distention, and study center. Randomization must be completed within 24 h of study enrollment. Treatment allocation will not be concealed from patients, physicians, or researchers at any point during the trial.

After obtaining preoperative informed consent, patients will be randomly assigned in a 1:1 ratio to the trial. The choice of the surgical technique (minimally invasive vs. open) and the method of reconstruction (primary anastomosis or discontinuous resection) during tumor resection, as well as the type of stoma (loop ileostomy, loop colostomy or cecal fistula) in the bridge-to-surgery group is at the discretion of the surgeon.

### Inclusion and exclusion criteria

Inclusion criteria:Patients with a left-sided colon or upper rectal tumor (from the splenic flexure to the intraperitoneal rectum with the tumor located more than 12 cm from the anal verge) undergoing curative treatmentThe tumor must be highly suspicious for colon cancer in CT or endoscopyColonic dilatation confirmed by CT or X-rayThe tumor, including potential metastases, must be deemed suitable for curative resection◦ Liver metastases must be deemed completely resectable (R0) during the primary tumor resection (subcapsular metastases or metastases requiring removal of no more than tree liver segments simultaneously with the primary tumor)◦ Pulmonary metastases that require maximum unilateral lobectomy for curative purposes without infiltration of the main bronchus or central pulmonary artery/veinPatients aged 18 years or olderWritten informed consent provided.No prior or concurrent malignancies within the 2 years preceding the enrollment

Exclusion criteria:Right-sided colon tumorExtraperitoneal rectal cancer of the lower and middle third (tumor located less than 12 cm from the anal verge)Life expectancy less than 120 daysLocally advanced tumor disease with local infiltration of adjacent structures that precludes R0 resection or necessitates neoadjuvant treatmentPatients receiving palliative treatmentEvidence of bowel perforation on CT or X-rayPatients deemed ineligible for surgery (ASA score ≥ IV)Lack of compliancePresence of addiction or other medical conditions that hinder the individual’s ability to comprehend the nature and consequences of the clinical trial.

### Intervention

The aim of the current study is to compare two surgical approaches for the resection of left-sided obstructive colon cancer: the single-stage emergency resection (control group) and the two-stage bridge-to-surgery procedure (intervention group). Both groups will undergo curative hemicolectomy, including tumor resection and lymph node dissection. International guidelines provide varying recommendations, with 42% advocating emergency surgery and 47% suggesting either emergency surgery or stenting as bridge-to-surgery. Primary resection with or without anastomosis is the most commonly recommended procedure [5]. Accordingly, emergency resection is currently the most frequently performed approach in many countries [19]. Retrospective studies have indicated that the two-stage approach with decompressing stoma can reduce 90-day mortality from 7.2 to 1.7% and the incidence of permanent stomas from 42 to 23% compared to the control group [18]. Considering these factors, we have determined the one-stage approach with emergency resection of the tumor to be the control group, reflecting the prevailing practice. Conversely, the two-stage procedure with decompression of the colon before elective surgery, as recommended by some guidelines, is assigned as the intervention group.

While the BTS approach can improve the patient’s general condition during resection, it also prolongs the time-to-surgery (TTS). Prolonged TTS may have an impact on cancer survival. Studies by Satish et al. and Kaltenmeier et al. have presented conflicting results, with Satish et al. suggesting that extended TTS (> 21–30 days) is associated with a lower adjusted risk of death [20], while Kaltenmeier et al. found that prolonged TTS is associated with an increased risk of death [21].

To address this potential issue, our study design incorporates TTS as a secondary end point and evaluate its association with cancer-specific factors, such as cancer survival.

#### Control group (emergency resection arm)

In the control group, patients will undergo a single-stage oncological left-sided hemicolectomy with the option of a primary anastomosis with or without loop ileostomy or a Hartmann’s procedure (closure of the colorectal stump and end colostomy).

#### Intervention group (decompressing stoma as bridge-to-surgery arm)

In the intervention group, patients will undergo a two-stage resection with a decompressing stoma procedure. After a period of convalescence, an elective, oncologic left hemicolectomy will be performed. The stoma technique during the first procedure can be performed as either loop or blowhole colostomy (a loop ileostomy is also possible if deemed adequate), while the elective resection can be conducted as a primary anastomosis with or without loop ileostomy or a Hartmann’s procedure. The time interval between the decompressing stoma and resection will be determined by the treating surgeon, with an expected period of approximately 30 days based on current studies [18, 22].

Any additional concurrent care, including the use of adjuvant therapy after resection, is left to the discretion of the treating physicians.

### Endpoints of the study

The study has identified several primary and secondary outcomes to evaluate the effectiveness and impact of the two surgical approaches for left-sided obstructive colon cancer. The primary outcome focuses on perioperative mortality within a 120-day period after surgery. Usually, perioperative death is defined as mortality within 90 days after surgery, but to compensate for the delay between decompressing stoma placement and tumor resection in the intervention group, we opted to extend the primary endpoint by 30 days according to recent studies [14, 18, 22].

Primary outcome:Perioperative 120-day mortality*Control group*: mortality within 120 days after emergency resection*Intervention group*: mortality within 120 days after decompressing stoma placement

Secondary outcomes:*Quality of life**Permanent Stoma rate**Stoma-associated complications**Quality-adjusted survival (QALY)**Number of resected lymph nodes**Number of R0 resections**3-year overall survival**3-year cancer-specific survival**3-year disease-free survival*

The secondary endpoints were developed in collaboration with experts as well as patient groups, such as the German ILCO, to ensure a comprehensive assessment of patient outcomes, including quality of life, complications, the rate of permanent stomas, and cancer-related factors.

### Statistics

The statistical analysis plan for the study involves various tests and methods to analyze different endpoints. The chi-squared test will be applied to compare the perioperative 120-day mortality between the control and intervention arms using an intent-to-treat analysis. The significance levels were set to 5% (two-sided). The secondary endpoints will each be analyzed accordingly: The rate of primary anastomoses, permanent stomas, and 120-day complication rate will be investigated using the chi-square test. The 3-year overall survival will be examined using the Kaplan-Meyer estimator combined with the log-rank test. The treatment effect on the patient-reported quality of life will be analyzed using a regression analysis. Quality-adjusted survival will be analyzed using marginal models and non-parametric regression.

The statistical significance of stratification factors will be assessed. Propensity score matching may be used as a part of a supplementary analysis, to control for potential confounding factors that were not accounted for during sampling. In particular, a propensity score matching procedure with age as a continuous variable may be used to control for between-arm age differences. Statistical analyses of matched-sub-cohorts will have an exploratory character, providing additional information about effect sizes. The standardized mean differences and confidence intervals will be reported, and *p*-values will be provided as an additional information.

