### Sample size calculations

The sample size calculation was performed using an estimated 120-day mortality rates of 8% and 1.7% in the control and intervention arms, respectively. These rates were extrapolated from the 90-day mortality rates of 1.7% (decompressing stoma (DS)) vs 7.2% (emergency resection (ER)) as well as the 3-year overall survival data in the propensity-score matched study by Veld, Tanis et al. [18]. The effect size was then reduced with an assumed 120-day mortality rate of 1.7% for the decompressing stoma group and 7% in the emergency resection group, resulting in a reduced effect size of 0.274 and an increased relative risk of 0.243.

To achieve the 80% power with a (two-sided) 5% significance level using a normal curve via arcsine transformation (Cohen, 1988, Chapter 6), at least 210 patients per arm (total 420 patients) need to be analyzed. To account for an expected 10% dropout rate, the target enrollment is 468 patients (234 per arm). Considering a 20% screen-failure rate, 588 patients will need to be assessed for eligibility. The power calculations were performed using SAS Version 9.4.

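### The primary mortality test ignores the age and ASA strata used in randomisation, and age differences are left to optional exploratory matching; the test is valid but slightly conservative

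*Protocol article*

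**What the plan says.** The Statistics section of the protocol article sets the primary analysis: "The chi-squared test will be applied to compare the perioperative 120-day mortality between the control and intervention arms using an intent-to-treat analysis". On the error rate it says "The significance levels were set to 5% (two-sided". No stratification factor enters this test.

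The sections on stratification and randomisation and on methods against bias list six factors used in allocation: age below or above 70, tumour stage, gender, ASA 1–2 versus 3, small bowel distention, and study centre. The Statistics section gives these factors one role, an assessment of their statistical significance. It names no stratified or adjusted estimate of the treatment effect.

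Age as a continuous variable appears only in a supplementary analysis: "a propensity score matching procedure with age as a continuous variable may be used to control for between-arm age differences". The same paragraph calls analyses of matched sub-cohorts exploratory.

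The sample size section contains no covariate adjustment. It uses an "assumed 120-day mortality rate of 1.7% for the decompressing stoma group and 7% in the emergency resection group", and concludes that "at least 210 patients per arm (total 420 patients) need to be analyzed".

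**The concern.** Stratifying allocation on a factor that predicts the outcome reduces the true variance of the difference between arms. An unadjusted test does not credit that reduction, so it rejects slightly less often than its nominal level and loses a little power. If allocation leaves some age imbalance, the unadjusted estimate carries it.

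The article's own figures show that age matters here. The Introduction reports 90-day mortality for "patients over 70 years of age (3.5% vs. 13.7" (per cent, decompressing stoma against emergency resection), while the rates at all ages were 1.7% and 7.2%.

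Matching suits the stated aim poorly. It discards randomised patients, and possibly deaths, from a trial that expects few deaths. A prespecified adjusted analysis would serve the same aim in the full intention-to-treat population. Testing whether stratification factors are significant does not adjust the treatment effect at all.

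**Working it through.** **1. The plan's own figure.** The inputs are 7% and 1.7% mortality, two-sided 5% and 80% power, from the sample size section.
- Effect size: h = 2·asin(√0.07) − 2·asin(√0.017) = 0.274. Relative risk: 0.017/0.07 = 0.243. Both agree with the article ("resulting in a reduced effect size of 0.274 and an increased relative risk of 0.243").
- Patients per arm: n = 2·((1.960 + 0.842)/h)² = 209.07, so 210. Power at 210 by the arcsine method is 80.2%. The stated size is reproduced.
- Expected deaths: 210 × 0.07 + 210 × 0.017 = 14.7 + 3.6, about 18.

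**2. Mortality by age group.** The article does not give the share of patients over 70, so I assume a range.
- The stoma-arm rates cap the share: 1.7/3.5 = 48.6%. I use 35% to 48%.
- The over-70 control rate is scaled to the 7% planning rate: 13.7 × 7/7.2 = 13.3%. The over-70 stoma rate stays at 3.5%.
- The rate at 70 or below follows from the overall rate. Example with 40% over 70: control (7 − 0.4 × 13.32)/0.6 = 2.79%; stoma (1.7 − 0.4 × 3.5)/0.6 = 0.5%.

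**3. Chi-squared against CMH by simulation, 210 per arm, strata balanced.** There were 200,000 runs for age strata and 60,000 for 16 strata. The 16 strata cross age, ASA and two further factors, with assumed odds ratios of 3–8 for age, 2–4 for ASA and 1–2 for each of the others.

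| Setting | Chi-squared power | CMH power | Gain (points) |
|---|---|---|---|
| Age only, 35–48% over 70 | 79.5–79.8% | 80.0–80.8% | 0.6–1.2 |
| 16 strata | 79.5–80.1% | 79.9–82.1% | 0.4–2.0 |

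Under no treatment effect, across all these settings, the true error is 4.1–4.7% for chi-squared and 4.7–5.0% for CMH. A logistic score test with four main effects changed power by −0.5 to +2.5 points, with a simulation error of about 1 point.

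**4. If age falls by simple randomisation.** With the same age-only inputs and no balancing, the chi-squared error is 4.7–5.0%. The unadjusted test is then close to nominal and not inflated.

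**5. How many factors the data can carry.** Age, gender, ASA and small bowel distention give 2 × 2 × 2 × 2 = 16 cells. With tumour stage at an assumed 2–4 levels there are 32–64 cells. Crossed with the 66 committed hospitals, there are 2,112–4,224 cells for 420 patients and about 18 deaths. Adjusting for everything is not possible.

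**The case against.** **The planned test is sound.** It holds its error at or below 5% and reaches about 80% power, so the sample size is met without adjustment. This stands, and it limits the point to an efficiency gain of about 0.5–2 points of power.

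**Age is already protected by stratified randomisation.** This stands in part. Stratifying at 70 controls imbalance across that cut but not within age bands. The article also does not say how six factors, centre included, are combined. If they are fully crossed, most blocks would never fill and balance on age could be much weaker than intended. That depends on an unstated detail, so I do not count it as a defect.

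**A reader might infer that the unadjusted test has an inflated error rate which adjustment would restore.** The documents do not support this. An error above 5% appears only if one conditions on a large chance imbalance, such as 55% against 45% over 70. Even under simple randomisation, a gap of 10 points or more arises in only about 4.6% of trials. With 110 against 100 patients over 70, the error is still about 4.8%. A bias figure based on the spread of age under unstratified allocation would likewise set aside the planned stratification.

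**A reader might also infer that matching could displace the primary result.** It could not. The article labels it supplementary and exploratory, and the primary test is fixed.

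**The unshown analysis plan may add adjusted analyses.** It may, but the article itself fixes the primary test as unadjusted, and that choice is what is questioned here.

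**Conclusion.** The point holds as a modest improvement. The primary test is valid and adequately powered, but it does not use the factors by which the trial randomises. The cost is a true error of about 4.1–4.7% instead of 5%, roughly 0.5–2 points of power, and an estimate that keeps any residual age imbalance. The one planned analysis aimed at age differences is optional and drops randomised patients.

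The sizes rest on the planning rates of 7% and 1.7%, on 90-day age-specific rates from a retrospective study carried over to 120 days, on an assumed 35–48% of patients over 70, and on assumed odds ratios for ASA and the other factors. Weaker prognostic factors would shrink the gain towards zero.

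**What to change.** - **Primary test:** a prespecified CMH test of 120-day mortality, stratified by age group (≤70 / >70) and ASA (1–2 versus 3), with a stratified risk difference and 95% CI in the intention-to-treat population.
- **Sensitivity analysis:** keep the unadjusted chi-squared test.
- **Supplementary analysis:** replace the propensity score matching with a prespecified analysis adjusted for continuous age in the full intention-to-treat population, using a sparse-data method such as penalised logistic regression.
- **Delete** the significance testing of stratification factors.
- **Keep the list short:** do not adjust for all six factors or for centre, given about 18 expected deaths.

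The sample size need not change, and age and ASA are already recorded for randomisation. The cost is revised wording, minor extra analysis work, and the ethics approval and registry note that the article requires for protocol changes. The change should be made before anyone on the trial team sees outcomes by arm, because in an open-label trial a later switch would look data-driven.
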